### Implementation {16c}

Randomization will occur at the patient level. Participants enroll in the trial and undergo screening and baseline assessments. Once patients have consented to participate and provided baseline data, they will be randomized to either the intervention group or the TAU group in a 1:1 ratio. The study administrators will conduct the randomization in the DIRECT admin panel after the baseline assessment is completed.

## Assignment of interventions: blinding

### Who will be blinded {17a}

Due to the nature of psychotherapeutic intervention trials, neither participants nor therapists can be blinded to treatment allocation. Biostatisticians remain blinded to allocation.

### Procedure for unblinding if needed {17b}

N/a: As blinding is not possible due to the study design, unblinding will not be needed.

## Data collection and management

### Plans for assessment and collection of outcomes {18a}

Our study focuses on postpartum depressive symptoms as the primary outcome, with secondary measures including mother–child bonding, self-efficacy, stress, app quality, and healthcare utilization. Other measures encompass sociodemographic, clinical, and pregnancy-related variables. Outcomes will be measured by self-reported questionnaires, which are assessed at baseline (t0), after completion of the intervention 6 weeks after allocation (IG) or 6 weeks after allocation (TAU) (t1), and at 12 weeks (t2) and 6 months (t3) after allocation. Participants who receive the intervention will also complete an intermediate assessment before session 4 (t0_1) and session 8 (t0_2). All questionnaires will be presented via the DIRECT app that also hosts the intervention. A detailed overview of all assessments can be found in Table 2.

**Table 2 Tab2:** Schedule of enrolment, interventions, and assessments

**Time point**		**Study period**							
		**Enrollment**	**Baseline**	**Allocation**	**Post-allocation**				
		(− t1)	(t0)	(0)	(t0_1) Session 4, ~ week 2	(t0_2) Session 8, ~ week 4	(t1) After completion, ~ week 6	(t2) Follow-up, week 12	(t3) Follow-up, week 24
**Enrolment**									
	Eligibility screening	X							
	Informed consent	X							
	Study suitability	X							
	Allocation			X					
**Interventions**									
	Smart-e-Moms				X	X	X	X	X
	TAU						X	X	X
**Assessments**	EPDS	X	X		X	X	X	X	X
	PBQ-16		X				X	X	X
	GSE		X				X	X	X
	Stress		X		X	X	X	X	X
	uMARS						X		
	App utilization						X		
	FIMPsy (adapted)		X				X	X	X
	Sociodemographic and clinical data		X						
	Birth-related data		X						
	City BiTS		X						
	CTS		X						
	PATHEV		X						
	WAI-SR				X	X	X		

*TAU* Treatment as usual, *EPDS* Edinburgh postnatal depression scale, *PBQ-16* Postpartum Bonding questionnaire, *GSE* Self-efficacy expectancy questionnaire, *Stress* Perkhofer stress scale, *uMARS* User version of the mobile application rating scale, *FIMPsy (adapted)* Questionnaire for the assessment of medical and non-medical resource utilisation in mental disorders, *City BiTS* City birth trauma scale, *CTS* Childhood trauma screener, *PATHEV* Patient questionnaire on therapy expectation and evaluation, *WAI-SR* Working alliance inventory—short revised

### Plans to promote participant retention and complete follow-up {18b}

Participants will receive push-up notifications that questionnaires are available in the app and will be reminded once if they do not complete the assessment. Participants who discontinue working on the sessions will still be invited to participate in the assessments. They will receive a monetary incentive to complete assessments. Participants in the intervention group will receive €15 for completing the 3-month follow-up assessment and an additional €25 for completing the 6-month follow-up assessment. Participants in the TAU group will receive €15 for completing the 6-week post-intervention assessment, an additional €15 for completing the 3-month follow-up assessment, and an additional €45 for completing the 6-month follow-up assessment.

### Data management {19}

All data is gathered online and will be recorded automatically by the DIRECT app. There are several measures in place to ensure data quality and safety. All questionnaires are tested beforehand to ensure correctness and completeness. The assessments are conducted automatically within the app, which ensures that questions are not skipped accidentally. Answers are synched with the server immediately or are stored locally for later synchronization in cases of internet disconnects. The data assessment and export features of the system have been tested in several studies and have proven to be reliable and robust. All admin personnel will receive technical training in working with the system to ensure all data collection processes are conducted and monitored according to the protocol.

Part of the anonymized data is made publicly available on an internet database for open access documentation. Before selecting the data, consultation with the data protection officer will take place.

### Confidentiality {27}

Participants will register on the DIRECT app with their e-mail address and telephone number to receive reminders, recover their accounts, and contact them in case of emergency. All data is stored on a secure server, and personal data will only be accessible to the supervising therapist and the study team. Personal data will be stored separately from questionnaire data to ensure data safety.

The data is saved locally on the smartphone device and is protected via the app password and any safety measurement the participants are using on their own device. The data is synchronized through encrypted (SSL) data transfer to a server (location: Germany). The server is provided by Hetzner GmbH, an ISO 27001 hosting provider that ensures compliance with the EU General Data Protection Regulation (GDPR). The data needs to be sent and stored on a server to ensure that clinical staff can support participants via the admin panel. Access to the admin panel is protected through two-factor authentication. Data export is only possible for study coordinators and again protected by two-factor authentication. The data export is pseudonymized by assigning an internal ID (hash). No personal data is exported. Study IDs and personal data are not matched outside of the admin panel. Data will be deleted upon request by participants (following GDPR regulations). Upon completion of the trial, all data will be exported and securely stored on an encrypted device for 10 years following good practice guidelines for clinical trials. This data will not contain personal information. After completion of the study with the follow-up assessments, all data from the app and the servers will be deleted.

### Plans for collection, laboratory evaluation, and storage of biological specimens for genetic or molecular analysis in this trial/future use {33}

N/a: No biological specimens will be collected.

## Statistical methods

### Statistical methods for primary and secondary outcomes {20a}

It is possible that some participants may not utilize the app, despite being assigned to the intervention group, and yet still participate in the surveys (non-compliance). We will deal with non-compliance in the analyses in two different ways. For the primary analyses, we will include data from all randomized patients and evaluate both (1) the effect of assignment to the intervention and (2) the effect of the intervention itself. For the estimation of the causal effect of the assignment to intervention on the primary and secondary endpoints (intention-to-treat analysis), the mean values between the two study groups at T1, T2, and T3 will be compared using *t*-tests and MANOVAs within the framework of structural equation models (SEM). For estimating the causal effect of the intervention itself on the primary and secondary endpoints, we treat all participants who were assigned to the intervention group but did not use the app (and did not drop out before the measurement of the first endpoint) as members of the control group (as-treated analysis). As this invalidates randomization, we will control for selection bias by adding the variables measured at baseline as covariates in the model. We assess all endpoints also at baseline, as this helps to assure the ignorability assumption (e.g., Cook, Steiner, & Pohl, 2010). Assumptions on distribution and homoscedasticity are tested and, if violated, relaxed (by using respective estimators or multi-group modeling).

To investigate the utilization of care services, means on individual items of the FIMPsy will be compared between the two treatment groups via *t*-tests in SEM.

For the intervention group, usability and acceptance of the intervention are analyzed using descriptive statistics to describe satisfaction (CSQ-i, SUS) and utilization behavior. The different recruitment channels for the intervention are surveyed and descriptively analyzed.

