### Outcomes {12}

#### Primary outcome measures

Edinburgh Postpartum Depression Scale (EPDS, [39]).

The primary outcome of the intervention will be the reduction of postpartum depressive symptoms, as measured by the Edinburgh Postpartum Depression Scale [39]. The self-report questionnaire consists of 10 items which are rated from 0 to 3 and summed to determine the overall score. A score of 9.5 or above is indicative of probable depression. The EPDS includes one item to assess suicidal ideation and self-harm tendencies that will be used to monitor potential self-harm throughout the intervention. The EPDS has demonstrated satisfactory validity and reliability and is the most commonly used outcome measure to assess postpartum depression. The German version of the EPDS has good psychometric properties [40]. The mean change from baseline will be compared between the intervention and the control group at post-assessment (t1), which is the most relevant time point of interest, and at follow-ups 1 and 2.

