### Sample size {14}

To ensure sufficient power for the effects at all time points, we considered potential dropout and power analysis for the last follow-up time point after 6 months (T3) using G*power. Dropout for patients with a depressive disorder in IBIs over the course of 6 months was estimated to be 50% based on previous literature [53]. For smartphone-based interventions targeting depressive symptoms, meta-analyses found small (*g* = 0.28, [54]) to small-to-moderate (*g* = 0.383, [55]) effect sizes when comparing apps to control conditions. As the TAU group in our study must be considered an informed TAU group due to the screening process, the calculation of our sample size is conservatively based on a small effect size (*d* = 0.3). The sample size calculation is conservatively based on a small effect size (*d* = 0.3), as the TAU group must be considered an informed TAU group due to the screening process. To find this effect in a randomized controlled trial with a one-tailed *t*-test (alpha error level = 5%, power = 0.80) for independent samples, *n* = 139 participants per treatment group (total *n* = 278 participants) are needed to complete the t3 assessment. Considering the dropout rate, a total sample of *N* = 556 participants is needed at the time of randomization (1:1 randomization: *n* = 278 participants in IG; *n* = 278 participants in TAU).

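### Two effects at three time points stand under the primary analysis of the EPDS, and no single test is named as the one that decides effectiveness

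*Protocol article*

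**What the plan says.** Section {20a} of the protocol article opens the analysis plan with "For the primary analyses, we will include data from all randomized patients and evaluate both (1) the effect of assignment to the intervention". The same sentence adds a second primary effect, that of the intervention itself. The first is estimated by intention to treat, comparing group means at T1, T2 and T3 with *t*-tests and MANOVAs in a structural equation model. The second moves intervention-group members who did not use the app into the control group. The section concedes that this breaks the randomisation, and it plans adjustment for baseline variables. Section {20c} lists the two effects as first and second but does not say which one carries the conclusion.

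Under the primary outcome in {12}, the EPDS change from baseline is compared at t1, "which is the most relevant time point of interest, and at follow-ups 1 and 2". The same sentence is attached to bonding, self-efficacy and stress, and in near-identical form to healthcare utilisation.

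An error level appears only in the sample size section {14}: "To find this effect in a randomized controlled trial with a one-tailed" *t*-test, with "alpha error level = 5%, power = 0.80". Section {20a} states no alpha, no testing order and no adjustment.

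**The concern.** The label primary covers two different effects, each at three time points, which makes six contrasts on the EPDS. The phrase about t1 ranks the time points by interest. It does not say that the trial's conclusion rests on t1, and since the secondary scales carry the same phrase it cannot serve as the designation of a confirmatory test.

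Two things are at stake. First, the error rate of an effectiveness claim depends on which of the six contrasts may support it, and the article does not say. Second, some quite possible results have no agreed reading: no effect at T1 but one at T3, or an effect only in the as-treated analysis. The second case matters more, because the as-treated contrast lacks the protection of randomisation.

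**Working it through.** **1. The plan's own figure.** Inputs from {14}: *d* = 0.3, one-sided alpha 0.05, power 0.80, 1:1 allocation, 50% dropout over six months.

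- Normal approximation: n per group = 2(1.645 + 0.842)² / 0.3² = 137.4, so 138.
- Exact noncentral *t*: 138.07, so 139 per group, with power 80.2%. This matches the article's 139.
- Dropout: 139 / (1 − 0.5) = 278 per group, 556 in total. This also matches.

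The calculation is therefore for one test at one-sided 5%.

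**2. Reference values.** For m independent tests at 5%, the family-wise error is 1 − 0.95^m: 14.3% for m = 3 and 26.5% for m = 6. The real tests are positively correlated, so the error is lower.

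**3. Correlated tests.** The article gives no correlations, so these are assumptions:

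- r is the correlation between EPDS test statistics at any two time points, taken as 0.5 to 0.9.
- k is the correlation between the intention-to-treat and as-treated statistics at the same time point. If a fraction q of the intervention group does not use the app, and non-use is random, k = √[(1 − q)/(1 + q)]. In whole persons out of 139, about 20% is 27 (q = 0.194, k = 0.82) and about 30% is 41 (q = 0.295, k = 0.74).
- Across different time points and different effects, the correlation is taken as r × k.

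Under no effect anywhere, the family-wise error is the probability that the largest of the normal statistics exceeds 1.645 (2 million draws per cell):

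| r | Three ITT tests | Six tests, 20% non-use | Six tests, 30% non-use |
|---|---|---|---|
| 0.5 | 11.9% | 16.9% | 17.8% |
| 0.6 | 11.1% | 15.8% | 16.8% |
| 0.7 | 10.3% | 14.7% | 15.5% |
| 0.8 | 9.3% | 13.3% | 14.1% |
| 0.9 | 8.0% | 11.5% | 12.2% |

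**4. If t1 alone decides and both effects stay primary.** Only two tests remain. The error is 6.3% at k = 0.95 and 8.1% at k = 0.70, and it cannot exceed 2 × 5% = 10% while both tests are valid.

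**5. What these figures leave out.** Every value assumes that the as-treated test has its nominal level. Any difference between users and non-users that the baseline covariates do not capture would move that level, and the article gives no basis for putting a number on it.

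**6. The alternative of keeping everything primary.** With Bonferroni at one-sided 5%:

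- Three tests at 0.0167 need 198 completers per group, or 2 × 198 / 0.5 = 792 randomised. With 139 per group, power per test is 64%.
- Six tests at 0.0083 need 235 per group, or 2 × 235 / 0.5 = 940 randomised. With 139 per group, power per test is 54%.

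**The case against.** The strongest reply is that the article does rank the time points, that the two effects answer different questions, and that nowhere does it say any one of six positive results would be enough. Multiplicity rules are often left to an analysis plan, which is not shown here. The planned MANOVAs might act as a joint test over time, although the article does not say what enters them.

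Much of this stands as a limit on size. A reader might infer that the false-positive rate is at least doubled. The documents do not support that as a floor. It fails for the three intention-to-treat tests once r reaches about 0.75, and it fails if t1 alone decides.

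A reader might also see a contradiction between t1 as the most relevant time point and a sample size in which the 139 per group "are needed to complete the t3 assessment". There is none. The stated reason is "To ensure sufficient power for the effects at all time points". Sizing for the visit with the heaviest dropout leaves t1 at least as well powered for the same effect size, and it does not nominate t3 as the decisive test.

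Finally, a reader might add a much larger error rate by supposing that non-users fare worse than users. That would need both an assumed direction and no covariate adjustment, whereas {20a} plans adjustment for baseline variables, including the baseline value of each endpoint. It would also measure bias in the as-treated estimate, not multiplicity.

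The reply does not remove the point itself. That both effects are primary is stated in {20a}, not left open. An analysis plan naming one intention-to-treat test would have to override that sentence.

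**Conclusion.** The concern holds in a limited form. The article puts the assignment effect and the as-treated effect under the primary analyses, assesses both on the EPDS at three time points, and fixes no decisive test.

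The size depends on the reading: roughly 11–18% if any of the six contrasts could count, 8–12% for the three intention-to-treat tests alone, and about 6–8% if t1 decides with both effects still primary. These ranges rest on assumed correlations, on random non-use, and on applying the one-sided 5% from the sample size section to every test, since the analysis section states no level.

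The missing interpretation of mixed results does not depend on any of these assumptions. The change should be made before the data are analysed. It does not call the sample size into question.

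**What to change.** In {12} and {20a}, name one confirmatory test: the intention-to-treat effect on EPDS at T1. Test T2 at the same alpha only if T1 is significant, and T3 only if T2 is significant. State that alpha and its sidedness in {20a}. Describe the as-treated (compliance-adjusted) effect, the MANOVAs and all secondary scales as supportive, and align {20c} with this.

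The cost is wording only. A fixed sequence needs no split of alpha, so 139 completers per group and 556 randomised remain adequate on the article's own assumptions. The downside is that T2 and T3 are confirmatory only if T1 succeeds, so an effect that emerges late would be reported as exploratory.

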### Methods in analysis to handle protocol non-adherence and any statistical methods to handle missing data {20c}

#### Dropout

To deal with missing data due to dropout, analyses are conducted in the context of structural equation modeling and estimated by full information maximum likelihood using all variables measured at baseline as auxiliary variables.

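### The primary EPDS comparison is stated as two different tests (change from baseline and raw means), and neither is the baseline-adjusted analysis that the collected data allow at no cost

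*Protocol article*

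**What the plan says.** Two sections of the protocol article describe the primary comparison.

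- **Primary outcome measures, under Outcomes {12}:** "The mean change from baseline will be compared between the intervention and the control group at post-assessment (t1"; the sentence goes on to single out t1 as the time point that matters most and adds both follow-ups. The bonding, self-efficacy and stress scales are defined in the same way.
- **Statistical methods {20a}, intention to treat:** "the mean values between the two study groups at T1, T2, and T3 will be compared using" t-tests and MANOVAs within structural equation models. Change scores are not mentioned and no covariate is named.

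Baseline measurements appear elsewhere in other roles.

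- **Dropout {20c}:** the models are "estimated by full information maximum likelihood using all variables measured at baseline as auxiliary variables".
- **As-treated analysis, also in {20a}:** "As this invalidates randomization, we will control for selection bias by adding the variables measured at baseline as covariates in the model". This analysis sits under the primary analyses too, which "evaluate both (1) the effect of assignment to the intervention and (2) the effect of the intervention itself".
- **Availability:** "We assess all endpoints also at baseline, as this helps to assure the ignorability assumption". Table 2 confirms EPDS at t0 for all participants.

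The sample size section {14} uses d = 0.3 and a one-tailed t-test for independent samples, without a covariate.

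**The concern.** A difference in change scores and a difference in follow-up means are two estimators with different variances, so the same data can give two p-values. The article does not say which one decides the primary result. The trial is open-label with a self-reported outcome, so it is better that no such choice remains once data are seen.

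Neither version is the efficient one. A raw-means comparison does not use baseline EPDS for the treatment effect. A change score uses it with a fixed coefficient of 1, whatever the true relation is. Regressing follow-up EPDS on arm and baseline EPDS estimates that coefficient, removes chance baseline imbalance, and in large samples is at least as precise as either. The article plans baseline covariates for the as-treated analysis but names none for the randomised comparison.

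**Working it through.** **Inputs.** From Sample size {14}: d = 0.3, one-sided alpha 0.05, power 0.80, 139 completers per arm at t3, 50% dropout, 556 randomised. The correlation r between baseline and follow-up EPDS is not given, so it is an assumption, shown from 0.3 to 0.7. The scale of d is not given either; it is taken in follow-up SD units.

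**1. The plan's own figure.** For a two-sample t-test the noncentrality is d·√(n/2) = 0.3 × √69.5 = 2.50, with 276 degrees of freedom. One-sided power at n = 139 is 0.802, and 139 is the smallest n that reaches 0.80. Dropout: 278 / (1 − 0.5) = 556. Both stated numbers reproduce for an unadjusted comparison of raw means.

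**2. Variance of each estimator relative to raw means.**

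- Raw means, completers only: 1
- Raw means by full information maximum likelihood, baseline EPDS as auxiliary, 50% missing completely at random: 1 − 0.5r²
- Change score, equal SDs at baseline and follow-up: 2(1 − r)
- Baseline-adjusted (ANCOVA): 1 − r²

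**3. One-sided power at 139 completers per arm**, using effective d = 0.3/√(relative variance):

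| r (assumed) | Raw means | Planned likelihood with auxiliary | Change score | Baseline-adjusted | Adjusted minus planned |
|---|---|---|---|---|---|
| 0.3 | 80.2% | 81.8% | 67.9% | 83.4% | 1.6 |
| 0.4 | 80.2% | 83.1% | 73.7% | 85.9% | 2.8 |
| 0.5 | 80.2% | 84.7% | 80.2% | 89.2% | 4.5 |
| 0.6 | 80.2% | 86.7% | 87.4% | 93.0% | 6.3 |
| 0.7 | 80.2% | 89.0% | 94.2% | 96.8% | 7.8 |

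A simulation at r = 0.5 (4,000 runs) gave relative variances of 1.02, 0.88, 0.98 and 0.75 in the same order. All four methods estimated a difference of about 0.30.

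**4. How often the two stated tests disagree.** With equal SDs and complete data, the two test statistics correlate at √((1 − r)/2). Using the normal approximation, P(disagree) = P(raw significant) + P(change significant) − 2·P(both):

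- r = 0.3: 0.804 + 0.680 − 2 × 0.615 = about 0.26
- r = 0.5: 0.804 + 0.804 − 2 × 0.693 = about 0.22
- r = 0.7: 0.804 + 0.943 − 2 × 0.774 = about 0.20

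**5. Is the low change-score power at r below 0.5 real?** Let k be baseline SD divided by follow-up SD. The general variance ratio of change to raw is 1 + k² − 2rk, so the break-even is r = k/2; it is 0.5 only when k = 1. Entry requires EPDS of at least 10. That truncation lowers r but also shrinks the baseline SD. As an illustration, take an untruncated correlation of 0.5 and cut the baseline at its mean: r falls to about 0.33 and k to about 0.66. The ratio is then 1 + 0.436 − 2 × 0.33 × 0.66 = 1.00, the same variance as raw means. At k = 0.6 and r = 0.3 the ratio is 1 + 0.36 − 0.36 = 1.00 and power is 80%. The 67.9% and 73.7% entries therefore depend on equal SDs. The adjusted and likelihood columns depend on r but not on k.

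**6. What the auxiliary variable does.** It predicts missing follow-up scores from baseline, and so recovers half of the r² variance reduction at 50% dropout. With complete data it returns the unadjusted difference, so a chance difference in baseline EPDS between the arms stays in the estimate.

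**The case against.** The best defence reads the two sections together: the methods section compares means of the endpoints, and the outcomes section defines the endpoint as change from baseline. On that reading only one test is planned. It is possible, but the methods text speaks of values at T1, T2 and T3 and never of change, so an analyst could follow either section in good faith.

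A second defence is that an unadjusted comparison in a randomised trial is valid, that the sample size matches it, and that a covariate set is often left to a separate analysis plan. This stands: no bias is involved, and lack of adjustment alone would be a matter of efficiency. An analysis plan could settle the model, but it would have to depart from one of the two statements in the article.

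Three stronger readings are tempting and not supported.

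- **That the two definitions are incompatible or estimate different effects.** Under randomisation they share the same expected difference and differ in variance and in sensitivity to baseline imbalance.
- **That the trial falls below 80% power if change scores are used, because the entry threshold makes r low.** Step 5 shows that the truncation which lowers r also lowers the baseline SD, so no shortfall follows. The article also does not say whether d = 0.3 is in change or follow-up units; in change units power is 80% by construction. And 139 is the t3 completer number, whereas t1 retention is not stated.
- **That baseline information is ignored throughout.** The as-treated analysis adjusts for it, and the likelihood method recovers part of it under dropout.

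**Conclusion.** The point holds as a free improvement. The article states two different tests for its primary outcome, which can disagree in roughly a fifth to a quarter of trials under the stated assumptions (normal scores, equal SDs, complete data, d = 0.3, 139 per arm). Baseline adjustment of the intention-to-treat comparison would add about 2 to 5 points of power over the planned likelihood analysis at r = 0.3 to 0.5, and about 8 at r = 0.7. Those gains assume r, 50% dropout completely at random and the t3 completer number; the gain at T1 cannot be computed from the article. The 556 is correct for the unadjusted raw-means test, and no loss below the stated 80% is demonstrated.

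**What to change.** State one intention-to-treat contrast, in the same words, in Outcomes {12} and Statistical methods {20a}: the between-arm difference in EPDS at T1, from a regression of EPDS on arm and baseline EPDS within the planned structural equation model, estimated by full information maximum likelihood for all randomised women. Give T2 and T3 in the same form. Adjust each secondary scale that is measured at t0 for its own baseline. This replaces both the change-score wording and the unadjusted-mean wording; the other baseline variables can remain as auxiliaries.

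The cost is a wording amendment made before the outcome data are analysed. No new data, visits or participants are needed, because Table 2 already schedules EPDS at baseline for everyone. The sample size can stay as it is.

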### Criteria for discontinuing or modifying allocated interventions {11b}

Participants can leave the study at any time for any reason if they wish to do so without any consequences.

Engagement in the program (i.e., starting and/or completion of sessions) will be automatically logged. After 1 week without starting or completing a new session, participants will receive a reminder message. Participants will still be invited to fill out all assessments even if they discontinue working on the sessions.

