#### Protocol non-adherence

We handle protocol non-adherence in two ways: First, we estimate the causal effect of the assignment to the intervention on the endpoints (intention-to-treat analyses); second, we estimate the causal effect of the intervention on the endpoints by using the actual intervention taken (as-treated analyses) and accounting for selection bias via covariates in the analysis.

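### An as-treated contrast that gives up randomisation stands beside ITT as a primary analysis; it may be biased, and ITT should be the sole primary

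*Protocol article*

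**What the plan says.** Section {20a} of the protocol article says that the primary analyses will include all randomised women and "evaluate both (1) the effect of assignment to the intervention and (2) the effect of the intervention itself". The first is ITT. For the second, "we treat all participants who were assigned to the intervention group but did not use the app" as controls. A bracketed condition limits the move to non-users who remain under observation: "and did not drop out before the measurement of the first endpoint) as members of the control group (as-treated analysis".

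The section acknowledges the consequence: "As this invalidates randomization, we will control for selection bias by adding the variables measured at baseline as covariates in the model". It names the assumption it needs and what supports it: "We assess all endpoints also at baseline, as this helps to assure the ignorability assumption". The Protocol non-adherence paragraph under {20c} repeats the plan: "by using the actual intervention taken (as-treated analyses) and accounting for selection bias via covariates in the analysis".

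Neither place ranks the two estimates, and neither mentions an estimator based on randomisation for the effect of use. The data for one are collected. Section {11b} says "Engagement in the program (i.e., starting and/or completion of sessions) will be automatically logged", and women who stop working on the sessions are still invited to every assessment.

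**The concern.** App use is decided after randomisation. If women who use the app differ in prognosis from those who do not, and baseline variables do not fully capture the difference, moving non-users into the control group makes the app look better or worse than it is. With no ranking of the two estimates, a report could lead with a favourable as-treated result, labelled a primary causal effect, while ITT is null.

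The rule has two further gaps. It moves only non-users whose first endpoint is observed, so classification depends on outcome observation, and it does not say clearly where the other non-users go. It also gives no definition of use, although both arms download the same DIRECT app and answer their questionnaires in it.

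**Working it through.** **Inputs from the document.** Sample size {14}: d = 0.3, one-tailed 5% test, power 0.80, 139 completers per arm at t3, 50% dropout. Allocation is 1:1.

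**Inputs assumed.** The share of non-users q and the user-minus-non-user gap δ (in outcome SD, positive when users do better, remaining after covariates) are not in the document. I use q = 10% to 30% and δ = 0.2 to 0.3.

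**Planned size reproduced.** A one-sided independent-samples t-test needs 138.07, so 139 per arm; 139/(1 − 0.5) = 278 per arm; 2 × 278 = 556. This agrees with the protocol.

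**Bias with no true effect.** Set the TAU mean to 0. Randomisation makes the whole intervention group average 0 as well, so users have mean qδ and non-users −(1 − q)δ. The as-treated control group is TAU plus the non-users, with mean −q(1 − q)δ/(1 + q). Hence

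bias = qδ + q(1 − q)δ/(1 + q) = 2qδ/(1 + q).

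**Rejection rate.** With n = 139, SE = √(1/[n(1 − q)] + 1/[n(1 + q)]), and the one-sided rate is Φ(bias/SE − 1.645).

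| q | δ | bias (SD) | false-positive rate |
|---|---|---|---|
| 10% | 0.2 | 0.04 | 9% |
| 10% | 0.3 | 0.05 | 12% |
| 20% | 0.2 | 0.07 | 14% |
| 20% | 0.3 | 0.10 | 20% |
| 30% | 0.2 | 0.09 | 18% |
| 30% | 0.3 | 0.14 | 29% |

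Example, q = 20% and δ = 0.3: bias = 2 × 0.2 × 0.3/1.2 = 0.10. SE = √(1/111.2 + 1/166.8) = 0.122. Φ(0.817 − 1.645) = 0.20.

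The formula moves every non-user. Under the protocol's rule, q should be read as the share of non-users among intervention-group women with an observed outcome.

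**Simulation check.** This used 139 per arm, 4,000 runs per scenario, one measured baseline covariate that is adjusted for, one unmeasured prognostic factor moderately driving use, no TAU access and no missing data.
- No true effect: adjusted as-treated gave 0.06, 0.10 and 0.13 SD at 10%, 20% and 30% non-use, with type I error 16%, 27% and 37%. The error is higher than in the table for a similar bias because adjustment shrinks the residual variance but not this bias. CACE by two-stage least squares was centred on 0, with type I error 5.0% to 5.6%.
- True effect 0.30 among users: as-treated gave 0.40 and 0.43 at 20% and 30% non-use; CACE gave 0.30.
- No unmeasured driver: adjusted as-treated was unbiased, with null rejection of 4.9% to 5.3% at 10% to 30% non-use. It was also more powerful than CACE: with a true effect of 0.30 it rejected in 92% against 81% of runs at 20% non-use, and 91% against 71% at 30%.

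**The case against.** The protocol is open about the problem. It labels the analysis as-treated, states that randomisation is lost, names ignorability and lists ITT first. Table 2 schedules a rich baseline: EPDS, bonding, stress, self-efficacy, treatment expectation, birth trauma, childhood trauma, service use and sociodemographics. Never starting the app is decided close to baseline, where such adjustment works best; later events such as illness or changing mood explain stopping midway better than never starting. All of this stands. It means that bias is possible, not established.

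CACE also has assumptions of its own. Its exclusion restriction says that assignment does nothing for women who do not use the sessions, yet {11a} assigns every intervention participant a therapist and {11b} sends reminders after a week without a session. That TAU has no access is inferred, not stated. Missingness may differ by arm, since {18b} pays only TAU at 6 weeks and pays TAU more at 6 months (€45 against €25). This too stands, and it is why CACE should be supportive and not primary.

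A reader might infer that a never-user who drops out before t1 is analysed as treated. The document does not say so. The parenthesis may only restate that non-compliers are women who skip the app but still answer surveys, and women without an outcome add almost no information in any case. It is an ambiguity to close.

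What the objection does not answer is why a contrast that depends on an untestable assumption should share primary status with one that does not.

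**Conclusion.** The concern holds as a matter of status and definition. The protocol gives equal primary standing to ITT and to a contrast that may be confounded, and it does not clearly fix who is reclassified. Under the assumed ranges the bias is about 0.04 to 0.14 SD, or roughly 12% to 46% of the planned 0.3 (0.036/0.3 and 0.138/0.3), with one-sided type I error of about 9% to 29% at 139 per arm. If non-users do better, the contrast hides benefit instead. If nothing unmeasured drives both use and outcome, there is no bias.

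Two stronger readings should be resisted. One is that the as-treated estimate is certainly confounded; the document cannot show this. The other is to quote rates for all 278 per arm (31% at q = 20% and 47% at q = 30%, both with δ = 0.3), which ignore the dropout that the protocol plans for. The ITT analysis is unaffected. The point should be fixed but does not undermine the trial.

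**What to change.** - In {20a} and {20c}, name ITT as the sole primary analysis.
- Report a complier-average causal effect, with randomised arm as the instrument for use, as the supportive estimate of the effect of use. It can be fitted in the planned structural equation framework.
- Define use, for example as at least one session started, and classify it from the automatic session log for every intervention-group participant, whether or not she later drops out.
- State the exclusion restriction, the assumption that TAU has no access to Smart-e-Moms, and the missing-data assumption.
- Keep the covariate-adjusted as-treated contrast at most as a labelled sensitivity analysis, and say where non-users without a t1 assessment are placed.

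The cost is wording and one additional model, with no new data. The CACE confidence interval will be wider than the as-treated one, and the estimate rests on its own assumptions.
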